### Participant timeline {13}

The patient-participant timeline was created according to SPIRIT guidelines [13] and is presented in Table 1. After receiving written consent from the patient-participants, eligibility screening, enrolment and allocation will be carried out by the research staff at least 1 week before the first clinical visit (T1). During the first clinical visit, the participants will be allocated to either the intervention group (Rehabkompassen®) or the control group (the PSC) for the structured follow-up. Data collected at the first clinical visit will be used as baseline in the statistical analyses. The various rehabilitation interventions will subsequently be carried out according to their clinical routines in the respective clinics. At the second clinical visit (T2), all patient-participants will receive the intervention by using Rehabkompassen® during their follow-ups.

We enrolled our first participant on 7 February 2022. We expect to enrol the final participant at the end of 2024. The total recruitment period will be 3 years. Approximately 40% and 45% of the sample will be recruited in 2023 and 2024, respectively. The 12-month follow-up will be completed at the end of 2025, followed by data analysis, manuscript preparation and submission in 2026 (Table 2).

**Table 2 Tab2:**

A GANTT schedule of the study

### Sample size {14}

The study is predicted to have 90% power in the analysis of both primary outcomes at a significance level of 2.5% for each individual test to account for planned correction for multiple comparisons with a target familywise error rate of 5%.

Sample size calculations were performed assuming a mean difference of 4 points in the SIS-p score between the groups at the 12-month follow-up. There is uncertainty regarding the minimum clinically important difference in the SIS-p, but differences in sizes between 10 and 15 points have previously been suggested [29]. A power analysis was conducted using Monte Carlo simulations, in which SIS-p data for the control group were generated from a beta distribution with *α* = 1.1 and *β* = 0.5, while Rehabkompassen® data were generated under the assumption of *α* = 1.1 and *β* = 0.385. This corresponds approximately to a mean value of 70 and a standard deviation of 28 for the control group, in line with what Guidetti et al. [25] reported for a population of stroke patients at 12 months after stroke. Under these assumptions, the results showed that we need to include 940 patients to detect a statistically significant difference in the SIS-p score when using an ordinal proportional odds model to compare the groups at the 12-month follow-up. The average odds ratio across all simulations was 1.5, as estimated using the function *orm* from the R package *rms* for comparing the intervention group to the control group [40]*.*

The sample size calculation for the mRS score was based on aggregated unpublished data from the Swedish Stroke Register (Riksstroke). The marginal distribution of mRS scores collected 12 months after stroke among Swedish patients was *0: 22.4%*, *1: 18.0%*, *2: 18.0%*, *3: 16.8%*, *4: 11.1%*, *5: 4.3%* and *6: 9.4%*. The function *popower* from the package *Hmisc* [41] in the statistical software R was used to determine that a sample size of 940 patients (470 in each group) is sufficient to detect a true odds ratio of 0.67 at 90% power when using an ordinal proportional odds model to compare groups.

Thus, 940 patients should be sufficient for both primary outcomes. To account for a 15% loss to follow-up rate, we plan to recruit 1106 patients for the study (Fig. 3).

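### The SIS-p sample size is stated for a 4-point difference, but the simulated distributions differ by 5.3 points; at 4 points, 940 patients give about 64% power, not 90%.

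*Protocol article*

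**What the plan says.** The section Sample size {14} of the protocol article claims "90% power in the analysis of both primary outcomes at a significance level of 2.5% for each individual test". For SIS-p it opens with the target: "Sample size calculations were performed assuming a mean difference of 4 points in the SIS-p score between the groups". It then describes a Monte Carlo simulation. The "SIS-p data for the control group were generated from a beta distribution with" parameters 1.1 and 0.5, and the intervention data from one with parameters 1.1 and 0.385. Of the control distribution it says: "This corresponds approximately to a mean value of 70 and a standard deviation of 28 for the control group". The result is 940 evaluable patients under a proportional odds comparison at 12 months, with an average odds ratio of 1.5. A 15% allowance for loss to follow-up raises this to 1106.

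The section Statistical methods for primary and secondary outcomes {20a} makes all tests two-tailed, applies Holm–Bonferroni across the two primary outcomes, and adjusts the SIS-p model for site and for baseline SIS-p with natural cubic splines. The sample size text mentions no covariate.

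**The concern.** A beta distribution's mean follows directly from its two parameters, so the article prints enough to check its own target, and the two do not agree. The stated 4 points is close to 74.07 minus the rounded control mean of 70, but the simulated control mean is 68.75. That origin is a guess; the mismatch is not.

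SIS-p was made a primary outcome because the smRSq alone was judged too insensitive, so the size of effect that SIS-p can detect is central to its role. A reader who accepts 90% power at 4 points would treat a null SIS-p result as strong evidence against an effect of that size. As calculated, the trial would miss such an effect more than one time in three.

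**Working it through.** **Inputs, all from the protocol article.** Control Beta(1.1, 0.5); intervention Beta(1.1, 0.385); 470 evaluable per arm (940 in total, allocated 1:1); 2.5% per test; two-sided; proportional odds comparison at 12 months.

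**Step 1: the simulated difference.** The mean on the 0–100 scale is 100 × a/(a+b), and the SD is 100 × √[ab/((a+b)²(a+b+1))].

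- Control: 100 × 1.1/1.6 = 68.75, SD 28.7.
- Intervention: 100 × 1.1/1.485 = 74.07, SD 27.8.
- Difference: 74.07 − 68.75 = 5.32 points; 5.32/4 = 1.33.

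**Step 2: reproduce the plan's figure.** Data were simulated from the two printed distributions and compared with the Wilcoxon rank-sum test, which is the score test of the two-group proportional odds model. With 470 per arm at two-sided 0.025 (20,000 runs), power is 89.6%. Rounding the scores to 101 or 33 levels gives about 88%. Proportional odds fits on 33 levels (144 runs) give an average odds ratio of about 1.5. The protocol's sample size, power and odds ratio are therefore reproduced at 5.32 points, which argues against a misprint in the beta parameters.

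**Step 3: power at 4 points.** Keep control at Beta(1.1, 0.5), and keep 1.1 as the first intervention parameter. For a mean of 72.75 the second parameter is 1.1/0.7275 − 1.1 = 0.412. Power with 470 per arm at two-sided 0.025:

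| Scenario | Power |
|---|---|
| 68.75 vs 72.75, continuous scores | 64% |
| Same, 33-level scale | 61–62% |
| 70 vs 74 exactly (second parameters 0.471 and 0.386) | 67% |
| 68.75 vs 72.75, reached by changing the first parameter instead (1.335, 0.5) | 38% |

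The odds ratio in the first scenario, estimated by fits on the 33-level scale, is about 1.34.

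**Step 4: sample size for 90% at 4 points.** In the first scenario, 850 per arm gives 89.9% and 880 gives 90.4%. That is 1,700 to 1,760 evaluable patients, or about 2,000 to 2,070 recruited after dividing by 0.85.

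**Step 5: credit for baseline adjustment (assumed correlations).** The two-sided 2.5% critical value is 2.241. Unadjusted power of 63.6% (6,000-run simulation) implies an expected test statistic of 2.241 + 0.348 = 2.589. As an approximation, adjusting for a baseline with correlation r multiplies this by 1/√(1 − r²).

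- r = 0.5: 2.589 × 1.155 = 2.99, power about 77%.
- r = 0.6: 2.589 × 1.25 = 3.24, power about 84%.
- r = 0.7: 2.589 × 1.400 = 3.63, power about 92%.

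The protocol states no correlation, so these are illustrations.

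**The case against.** The strongest reply is that the calculation is sound on the scale that is analysed. The model is proportional odds, results are reported as odds ratios with confidence intervals, and the beta parameters, 940 patients, 90% power and odds ratio of 1.5 all agree with each other. On this view only a descriptive translation to the mean scale is wrong. That is right about where the error lies, and it is why the sample size need not change. But the 4 points is presented as the assumption behind the calculation, and 5.32 does not round to 4. Even 4.49 points, about the largest difference that would, gives only about 75% power.

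A second reply is that 64% describes an unadjusted test at 2.5%, not the planned analysis. This partly stands. Baseline adjustment could raise power substantially, and Holm–Bonferroni tests SIS-p at 5% if the smRSq has the smaller p-value and passes 2.5%, in which case unadjusted power at 4 points is about 74%. Neither is part of the stated calculation, which sizes each test at 2.5% without covariates.

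Third, a mean difference does not by itself fix the power of a rank-type test. That is true, and the figure depends on how 4 points is reached. Every unadjusted route tried stays far below 90%.

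Finally, the protocol cites 10 to 15 points as suggested important differences, so 4 and 5.3 both lie well below that range, and exclusion of an effect would properly be read from the confidence interval. This limits the clinical stakes but leaves the power statement wrong.

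**Conclusion.** The concern holds. The protocol's printed distributions imply a 5.32-point difference, and its sample size, power and odds ratio belong to that difference. At a true 4 points, 470 per arm gives about 64% power. This assumes an unadjusted comparison at two-sided 2.5%, a first beta parameter held at 1.1, and only the second intervention parameter changed. Other unadjusted routes at that level give 38% to 67%. Only an unstated baseline correlation of about 0.7 would bring power back to 90%. The smRSq calculation is unaffected: an odds ratio of 0.67 with 940 patients at 2.5% gives 89.4%.

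**What to change.** In Sample size {14}, state the SIS-p design effect as about 5.3 points (68.75 vs 74.07, average odds ratio about 1.5) at 90% power. Give the control mean as 68.75 rather than approximately 70, and add the power at 4 points: about 64%, unadjusted, at two-sided 2.5%. If 4 points is the intended target, rerun the simulation with an intervention second parameter of about 0.412 under the planned baseline-adjusted model, state the assumed baseline correlation, and report the power obtained.

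The cost is a revised paragraph and one simulation rerun. The stated detectable difference or power becomes less favourable; enrolment, the primary test and the control of the familywise error rate stay as they are.

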## Statistical methods

### Statistical methods for primary and secondary outcomes {20a}

Group differences in the mRS and SIS-p scores at the 12-month follow-up will be tested using ordinal logistic (proportional odds) regression, adjusted for site with fixed effects [43]. For the SIS-p score, models will also be adjusted for the baseline SIS-p score, with natural cubic splines to account for nonlinearity in the association. The results from the analyses will be presented as odds ratios with corresponding 95% confidence intervals and *p* values.

For the two primary outcomes, adjustments of the significance levels of the individual tests will be performed using the Holm–Bonferroni method to ensure that the familywise error rate will not be inflated above 0.05.

Secondary outcomes on an ordinal scale will be analysed similarly using ordinal logistic regression. All analyses will primarily be conducted in accordance with the intention-to-treat principle. As complementary analyses, per-protocol analyses will be performed using data from patients with full availability of primary variables and predefined criteria for adherence. Further details about the statistical analyses will be predefined and published in a separate statistical analysis plan. A data management plan has been established, providing details of the handling, organization and storage of study data.

A statistical significance level of *p* < 0.05 (two-tailed) will be applied to all analyses. For the two primary outcomes, adjustments of the significance levels of the individual tests will be performed using the Holm–Bonferroni method to ensure that the familywise error rate will not be inflated above 0.05.

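### The single figure of 940 includes deaths in the mRS calculation but needs a living respondent for every SIS-p score; if the 15% loss excludes deaths, SIS-p power is about 86%, not 90%

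*Protocol article*

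**What the plan says.** All of the following is in the protocol article.

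- **Power claim (Sample size {14}).** "The study is predicted to have 90% power in the analysis of both primary outcomes". Each of the two tests is planned at 2.5%, and Statistical methods {20a} makes them two-sided.
- **SIS-p (Sample size {14}).** The calculation is a simulation: "SIS-p data for the control group were generated from a beta distribution" with parameters 1.1 and 0.5, against 1.1 and 0.385 for the intervention group. Every simulated patient has a score, and the result is 940 patients.
- **mRS (Sample size {14}).** The calculation uses a stroke-register distribution at 12 months over seven categories, with 9.4% in category 6. It finds that "a sample size of 940 patients (470 in each group) is sufficient" for an odds ratio of 0.67.
- **Conclusion (Sample size {14}).** "Thus, 940 patients should be sufficient for both primary outcomes". A single inflation, for 15% attrition, then takes this figure to 1106.
- **Outcome definitions (Outcomes {12}, Primary outcome).** An smRSq score of 6 means death and is taken from medical records. SIS-D8 is reported by the participant on a scale from 0 to 100, and no value is assigned to death.

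**The concern.** A death is an observed result for one primary outcome and an absent one for the other. In the mRS calculation, category 6 lies among the 940 patients who remain after the 15% has been taken off, so on its face the 15% is loss other than death. The SIS-p calculation treats the same 940 as 940 completed scores. One number therefore stands for two populations, and no allowance links them.

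What is at stake is the stated power for a primary outcome. Neither calculation has slack: both reproduce at just under 90% with 940, so any shortfall in SIS-p scores takes power below the stated figure.

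**Working it through.** **Inputs.** From Sample size {14}: SIS-p Beta(1.1, 0.5) versus Beta(1.1, 0.385); mRS proportions 22.4, 18.0, 18.0, 16.8, 11.1, 4.3 and 9.4%; odds ratio 0.67; significance level 0.025 per test; N = 940; loss 15%. From Statistical methods {20a}: two-sided tests.

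**1. The plan's own figures reproduce.**

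- *mRS, Whitehead's proportional-odds formula.* V = n³ / [12(n+1)²] × (1 − Σp³). Here Σp³ = 0.0299, so with n = 940, V = 75.8 and √V = 8.71. Then |ln 0.67| × √V = 0.4005 × 8.71 = 3.487. Subtracting 2.241 leaves 1.246, which is power of 89.4%.
- *SIS-p, distributions.* The control mean is 100 × 1.1/1.6 = 68.75 with SD 28.7, against the stated approximate 70 and 28. The intervention mean is 100 × 1.1/1.485 = 74.1.
- *SIS-p, power.* The rank-sum test (the score test of the unadjusted proportional-odds model) on simulated data gives about 89% with 470 per group. Scores rounded to 33 levels give about 88%. The mean odds ratio is about 1.48, against the stated 1.5.
- *Recruitment.* 940 / 0.85 = 1105.9, that is 1106.

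**2. Reading A: deaths are inside the 940 and outside the 15%.** Deaths: 940 × 0.094 = 88. SIS-p scores: 940 × 0.906 = 852, or 426 per group. The same simulation then gives:

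| SIS-p scores | Continuous | 33 levels |
|---|---|---|
| 940 | about 89% | about 88% |
| 852 | about 86% | about 84% |

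The fall is 3 to 4 percentage points.

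**3. Reading A with lower mortality.** The article gives no mortality after enrolment, so these rates are assumptions. At 3%, 940 × 0.97 = 912 scores; at 5%, 940 × 0.95 = 893. Power on continuous scores is about 88% in both cases.

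**4. Reading B: the 15% already includes deaths.** SIS-p keeps 940 scores and about 89% power. smRSq is then available in more than 940, because deaths are scored from records. At the register rate, 1106 × 0.094 = 104 deaths, so n = 940 + 104 = 1044 and mRS power is 92.4%. The whole 15% is 1106 − 940 = 166 people, which leaves 166 − 104 = 62 (5.6% of 1106) for every other kind of loss.

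**5. Whether the mRS calculation needs redoing.** With category 6 removed and the rest rescaled to survivors, n = 940 gives 89.1%, against 89.4% as stated. It does not.

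**The case against.** **The article never says that deaths fall outside the 15%.** The Discussion reports 86% retention at 12 months in the pilot, close to an allowance of 15% for all attrition. The article does not say whether that figure counts deaths, but Reading B is plausible, and under it 940 is enough for both outcomes. This stands. A reader might infer that 940 is wrong on any reading; it is not.

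**The 9.4% is not a forecast for this trial.** It is a register figure counted from stroke onset. The trial enrols patients already discharged from acute care, within 4 months of onset, who can answer the questions. Early deaths cannot enrol, so 88 is probably too many. This also stands, and is why the 86% is conditional. But the plan relies on that same distribution for its mRS power, so on its own inputs the 9.4% belongs in both calculations.

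**The planned analysis is more powerful than the calculation.** Statistical methods {20a} adjusts SIS-p for its baseline. By the usual 1/(1 − r²) approximation, losing 9.4% is offset when r² = 0.094, a baseline correlation of about 0.31 (an assumption). Holm's step also tests SIS-p at 0.05 once smRSq is significant. With 852 scores, power is 0.859 at 0.025 and 0.913 at 0.05. If the two tests were independent (an assumption), SIS-p power would be 0.859 + (0.913 − 0.859) × 0.894 = 0.907. Either feature may recover the loss. Neither is credited in the stated calculation, which fixes 2.5% per test and ignores baseline, so they do not support the 90% as derived.

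**How deaths enter the SIS-p analysis can be left to the separate analysis plan.** Agreed. The point here is only the number and power that the sample size section itself states.

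**Conclusion.** The mismatch is real and lies within the sample size section: 940 includes deaths for one outcome and cannot include them for the other. Its size depends on something the article leaves open.

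- If the 15% excludes deaths and 9.4% applies: about 852 SIS-p scores and about 86% unadjusted power (about 84% on 33 levels), against the stated 90%.
- If the 15% excludes deaths and mortality after enrolment is 3 to 5% (assumed): about 88%.
- If the 15% includes deaths: 940 scores, about 89%, in line with the plan within simulation and rounding tolerance.

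A reader might go further and conclude that SIS-p is definitely underpowered, or that recruitment must rise to hold 940 SIS-p scores. The article supports neither: it does not define the 15%, gives no mortality after enrolment, and plans an analysis that may regain the loss. This is a modest correction to a stated power figure for a primary outcome, not a flaw in the design.

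**What to change.** In Sample size {14}:

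1. State whether the 15% loss covers deaths.
2. Give the analysable number and the power separately for smRSq and for SIS-p.
3. If the 15% does not cover deaths, restate SIS-p power as about 86% with about 852 scores on the plan's own inputs. If credit is wanted for baseline adjustment or the Holm step, say so and give the assumed correlation.

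The mRS calculation need not be rerun and the 1106 need not change. The cost is a few sentences and, on one reading, a slightly less favourable stated power.

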### Recruitment {15}

To achieve the target sample size, patients will be recruited from approximately 15 participating outpatient clinics throughout Sweden. The participating clinics have been and will be recruited either by personal contacts or after the study is promoted at the national and regional conferences.

To attract more clinics to participate in the study, the Chief Investigator will continuously promote the study at professional and lay-community conference/educational events. To attract more patients, recruitment posters with the contact details of research staff will be displayed at each participating site. All stroke survivors in the participating clinics will receive the study information and a letter inviting them to participate in the study. Other study awareness efforts, including clinical trial finder websites and word of mouth, will also be used to enhance the recruitment of clinics and participants. Moreover, recruitment status relative to planned targets will be reviewed monthly by the administrative study team, and the Chief Investigator will adjust the recruitment plans as needed.

## Assignment of interventions: allocation

### Sequence generation {16a}

The allocation sequence will be created centrally using computed-generated random numbers stratified by clinic. To reduce predictability, permuted block randomization will be used with random block sizes from 2 to 8 to ensure that participants are randomly assigned to the intervention or control group [42].

### Concealment mechanism {16b}

A statistician (the second author) who is not involved in outcome assessment or the patients’ treatment will generate the allocation sequence. The allocation sequence will be installed in REDCap, which will be concealed from the study personnel working in participant recruitment. The study personnel in each clinic will automatically receive an allocation decision with a study number when they register a new patient in REDCap.

### Implementation {16c}

Research staff at the local clinic will enrol participants via REDCap, which will automatically assign participants to either the control or intervention group.

## Assignment of interventions: blinding

### Who will be blinded {17a}

As in many rehabilitation intervention studies, this is an open-label study in which a double-blind intervention is not possible. Group allocation will be blinded in data analysis by two statisticians.

### Procedure for unblinding if needed {17b}

The design is open label with only data analysts being blinded so unblinding will not occur.

## Data collection and management

### Plans for assessment and collection of outcomes {18a}

We will use 6 validated and reliable PROMs as the outcome measurements in the study (see Table 1 and the “Outcomes {12}” section) to facilitate the development of patient-tailored rehabilitation regimens, strengthen patient-centred care and stitch together the currently fragmented post-acute continuum of care after stroke. To promote data quality, all clinical staff who participate in the study will be authorized, trained and competent according to the ethically approved protocol, the principle of Good Clinical Practice (GCP). The Chief Investigator and two research nurses will provide support whenever needed by clinical staff.

### Plans to promote participant retention and complete follow-up {18b}

We will employ several strategies to promote complete participant follow-up. A free clinical visit at approximately 12 months after stroke onset is an important promotor to enhance participant retention. Before the 3- and 12-month visits, an appointment date will be sent to the participants via regular mail, which will be followed by a phone call from research personnel. Moreover, all participants will receive the Rehabkompassen**®** questionnaires in their inbox at 1177.se. Directly after the 12-month visit, a feedback questionnaire will be provided digitally via 1177.se. If the response is not provided within a week, research personnel will make a phone call to remind the participants. In the case of no response, research personnel may call the participant again. For participants who experience technical difficulties, technical assistance will be provided by research personnel when needed. In addition, the option of video visits is also available in case a participant is not able to have a face-to-face visit.

